## Abstract

**Background:**

Early diagnosis of cerebral palsy (CP) is important to enable intervention at a time when neuroplasticity is at its highest. Current mean age at diagnosis is 13 months in Denmark. Recent research has documented that an early-diagnosis set-up can lower diagnostic age in high-risk infants. The aim of the current study is to lower diagnostic age of CP regardless of neonatal risk factors. Additionally, we want to investigate if an early intervention program added to standard care is superior to standard care alone.

**Methods:**

The current multicentre study CP-EDIT (Early Diagnosis and Intervention Trial) with the GO-PLAY intervention included (Goal Oriented ParentaL supported home ActivitY program), aims at testing the feasibility of an early diagnosis set-up and the GO-PLAY early intervention. CP-EDIT is a prospective cohort study, consecutively assessing approximately 500 infants at risk of CP. We will systematically collect data at inclusion (age 3–11 months) and follow a subset of participants (*n* = 300) with CP or at high risk of CP until the age of two years. The GO-PLAY early intervention will be tested in 80 infants with CP or high risk of CP.

Focus is on eight areas related to implementation and perspectives of the families: early cerebral magnetic resonance imaging (MRI), early genetic testing, implementation of the General Movements Assessment method, analysis of the GO-PLAY early intervention, parental perspective of early intervention and early diagnosis, early prediction of CP, and comparative analysis of the Hand Assessment for Infants, Hammersmith Infant Neurological Examination, MRI, and the General Movements method.

**Discussion:**

Early screening for CP is increasingly possible and an interim diagnosis of “high risk of CP” is recommended but not currently used in clinical care in Denmark. Additionally, there is a need to accelerate identification in mild or ambiguous cases to facilitate appropriate therapy early. Most studies on early diagnosis focus on identifying CP in infants below five months corrected age. Little is known about early diagnosis in the 50% of all CP cases that are discernible later in infancy. The current study aims at improving care of patients with CP even before they have an established diagnosis.

**Trial registration:**

ClinicalTrials.gov ID 22013292 (reg. date 31/MAR/2023) for the CP-EDIT cohort and ID 22041835 (reg. date 31/MAR/2023) for the GO-PLAY trial.

## Introduction

Cerebral palsy (CP) is the most common cause of lifelong motor impairment in children and is defined by the Surveillance of Cerebral Palsy in Europe (SCPE) as “a group of permanent but not unchanging disorders of movement and/or posture and of motor function, which are due to a non-progressive interference, lesion, or abnormality of the developing/immature brain” [1]. An early diagnosis is important in order to start relevant intervention, when neuroplasticity is highest [2]. Research suggests that early intervention programs have a positive influence on cognitive and motor outcomes and are a parental request [3].

In 2010 the Danish Cerebral Palsy Follow-up Program (CPOP) was introduced with the aim of establishing more standardized healthcare for children with CP [4]. The CPOP ensures that children with CP are followed annually and aims to document, monitor, and improve the quality of health care for children with CP in Denmark. A previous Danish national study from birth years 1995–2003 found that the median corrected diagnostic age of children with CP was 11 months based on first mention in the patient file [5]. In a recent study, the diagnostic age was 13 months for children with CP born in 2010–2013, based on the first registered diagnosis in The National Patient Registry [6].

The best predictive tools for early diagnosis of CP have been found to be the Prechtl Qualitative Assessment of General Movements (GMA) [7], Hammersmith Infant Neurological Examination (HINE) [8]and cerebral magnetic resonance imaging (MRI) [3]. These tools can be used to diagnose CP before the age of five months [3]. The method Hand Assessment for Infants (HAI) [9] has in recent publications been found promising to complement these tests, but little evidence on HAI has been published. Feasibility of an early-diagnosis set-up of a systematic approach with neurological assessment, GMA/HINE and neuroimaging has been evaluated in several studies [10–12], but not yet in Denmark, and not in a setting where both the newborn- and infant-detectable risk pathways were included. Neonates may have obvious risk factors for CP at birth/in the neonatal period. In the present study, we will also include infants without such risk factors. These children from the infant-detectable risk pathway present with clinical findings in the first year of life suggesting CP.

More than 80% of children with CP have abnormal brain imaging [13]. It has been recommended for many years to use MRI when diagnosing CP, even though CP remains a clinical diagnosis and MRI can be normal in a child with CP [3]. A systematic review from 2007 showed that the majority of MRIs gave clues to the pathogenesis of CP [14]. In a previous Australian study of children with CP, MRI patterns varied depending on parity, gestational age, level of neonatal care, Apgar score, and time to established respiration [15]. Diagnostic MRI of newborns and infants with suspected CP is based on images with the focus on identifying structural brain pathology, such as periventricular leukomalacia, maldevelopment, or grey/white matter damage.

Genetics is known to play an important role in the development of CP. Previous research with genetic testing has shown that genetic aetiology, while often seen in children with no previous gestational or neonatal risk factor, is not limited to this group nor those with other neurodevelopmental comorbidities such as epilepsy or intellectual disability [16]. One study has suggested an association between CP and genes that hinder early brain development and/or predispose to susceptibility to environmental risk factors [17]. Causes for the various CP subtypes, including the most prevalent spastic subtype and the rare ataxic or dyskinetic subtypes, are different. In some cases, the cause is obvious, such as asphyxia during labour, cerebral bleeding, or infection. In many cases the exact cause is unknown. However, in an increasing number of patients it is now possible to identify the underlying cause, since it has become clear that CP can be part of several genetic syndromes. Many treatable metabolic and genetic diseases such as dopa-responsive dystonia may be misdiagnosed as CP [18, 19]. Identifying a genetic cause makes it possible to provide genetic counselling and maybe a specific treatment, e.g., with nutrient-specific diets or medications, which can interrupt disease progression and prevent further injury. In the current study extensive genetic testing with whole genome sequencing will be performed in participants with definite CP or high risk of CP.

Receiving an early diagnosis of CP or high risk of CP is of high priority and parents and care providers agree that early access to interventions is important for the child [20]. Parents of children at risk of CP may experience high stress levels, depression, and chronic sorrow symptoms [21, 22]. Intensive home-based approaches addressing cognitive and motor improvement increasingly involve parents as treatment providers, supervised by therapists [23]. This can lead to both a positive parental outcome such as increased competences and motivation for care of the child, knowledge of the disease, as well as negative outcomes, because parents may be overwhelmed by the burden of responsibility and the feeling of insufficiency or lack of confidence [24].

The current study CP-EDIT (Early Diagnosis and Intervention Trial) with the GO-PLAY intervention included (Goal Oriented ParentaL supported home ActivitY program), aims to test the feasibility of an early diagnosis and intervention set-up in four neuropaediatric centers in Denmark with focus on eight areas related to implementation and the perspective of the families: early cerebral MRI, early genetic testing, implementation of the General Movements Assessment method, analysis of the GO-PLAY early intervention, parental perspective of early intervention, parental perspective of early diagnosis, early prediction of CP, and comparative analysis of the Hand Assessment for Infants method, Hammersmith Infant Neurological Examination, MRI, and the General Movements method.

### Availability of data and material

By contacting the corresponding author and upon reasonable request, de-identified data and standard operating procedures can be made available for the majority of the data if there can be established a data transfer agreement. The handling of data was approved by the local Data Protection Agency (j.nr.: P-2022-980). Protocol changes will be communicated to the research ethics committee and trial registry.

The study will be open for participant inclusion April 1^st^, 2023.

#### Dissemination

Findings regarding the CP-EDIT results will be communicated in line with a dissemination plan that will be develop by the steering committee, relevant stakeholders, decision makers, academia, to the public through dissemination activities including publications in peer-reviewed, international medical journals and to all included participants through the laymans summary.

#### Inclusion procedure and follow-up

A three-step procedure will be applied in order to identify as many infants with high risk of CP as possible before the age of 1 year.

##### The 1^st^ step

Newborns- and infants will be screened for eligibility in neonatal departments or when referred to the neuropaediatric clinic in one of the participating hospitals. Referral to the study can also be from parents or from other Danish paediatric departments. Inclusion criteria are listed in Table 1. Four Danish paediatric departments will participate (Copenhagen University Hospital—Rigshospitalet, Copenhagen University Hospital—Herlev, Aarhus University Hospital, and Aalborg University Hospital). Inclusion period is April 1st, 2023, to March 31st, 2025.

**Table 1 Tab1:** Inclusion criteria CP-EDIT study

Newborn-detectable pathway	Infant detectable pathway
1. Preterm birth with gestational age below 32 or birth weight < 1500 g and clinical concern 2. Moderate to severe brain injury (cystic periventricular leukomalacia, Papile grade 3 to 4 intraventricular haemorrhage, neonatal stroke, term hypoxic-ischaemic encephalopathy (≥ 35 weeks gestation at birth) or other significant neurological condition) 3. History with known risk factors for CP (e.g. neonatal seizures, meningitis, kernicterus, severe hypoglycaemia, brain malformation, increased tone, ExtraCorporal Membrane Oxygenation) 4. Parental concern and one of the factors above	1. Inability to sit independently by age 9 months 2. Hand function asymmetry or crawl asymmetry 3. Inability to take weight through the plantar surface of the feet 4. History with known risk factors for CP as in neonatal pathway 5. Parental concern and one of the factors above

Inclusion criteria are listed in Table 1.

Exclusion criteria are:Progressive or neurodegenerative disorders.Known genetic or disability disorders not associated with CP, for example Down syndrome.

Flow chart of the study is depicted in Fig. 1. If one of the inclusion criteria is present and no exclusion criteria is present at the time of screening, a member of local steering committee will be contacted by phone or mail. These children will define cohort I. We expect to screen approximately 500 children in this 1^st^ step.

**Fig. 1 Fig1:**
[figure not shown]
Flow-chart of the CP-EDIT study. Abbreviations: AIMS = Alberta infant motor scale; CP = cerebral palsy; GMA = general movements assessment; GMFCS = gross motor function classification system; HAI = hand assessment for infants; HINE = Hammersmith infant neurological examination; MACS = manual ability classification system; MRI = magnetic resonance imaging; n = number

##### The 2^nd^ step

A child will be invited for the first assessment if the members of local steering group consider that the child has an increased risk of CP and parents’ consent is present. Children, participating in the assessment, will define Cohort II. Expected number of assessed children is 300.

##### The 3^rd^ step

Participants from cohort II will be included in the follow-up study (cohort III who have high risk of CP or definitely CP) if they fulfil at least one of the requirements A or B:

A.any two of the following:A.1 Neuroimaging predictive of a motor disability including the involvement of one or more of the following structures: sensori-motor cortex, basal ganglia, posterior limb of the internal capsule, pyramidal tracts.A.2 GMA test with absent fidgety GMs at fidgety ageA.3 HINE scores < 57 at 3months or < 60 at 6months or < 63 at 9 months or < 66 at 12 monthsB.both of the following:B.1 Unilateral brain injury on neuroimaging (MRI or ultrasound) predictive of CPB.2 Clinical signs of asymmetry

The parents will be informed that a child has CP or has a high risk of CP. Approx. 160 children are expected to be included in the follow-up as high risk of CP or CP after the 1^st^ assessment.

Exclusion criteria from the 1^st^ step will be applied during the whole study. For example, if a child shows signs of progressive disorder at the age of 12 months and diagnosis becomes clear before the age of 18 months, the child will be moved from the CP-cohort (cohort III) to the non-CP group and not invited for further assessments in the CP-EDIT; the child will be classified as “no CP” at the age of 24 months.

Participants from cohort III from the two study sites at Aarhus and Aalborg hospitals will be included in the GO-PLAY randomized-controlled trial for children with CP or high risk of CP. Participation requires that parents talk sufficient Danish. We expect 60–80 participants in GO-PLAY.

After screening the definition of ‘Definitely CP’ encompasses participants that fulfil SCPE CP clinical criteria and guided by fulfilling the following: 4/5 for children < 5 months, and 3/4 for children ≥ 5 months of the following at screening.Delayed motor development without signs of neuromuscular disease (floppy infant, absent reflexes)GMA test with absent fidgety GMs at fidgety ageHINE scores < 57 at 3months or < 60 at 6months or < 63 at 9 months or < 66 at 12 monthsMRI or ultrasound of brain with a lesion in the abovementioned specific areasFocal neurological symptoms (hyperreflexia, clonus, dystonia, ataxia, intention tremor) or clinical signs of asymmetry

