##### Cohort III

Children with definite CP or high risk of CP. All participants are followed at ages 6, 12, 18 and 24 months and blood samples for whole genome sequencing is categorised as described below.

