#### Primary and secondary outcome measures

*MRI.* Primary results are a description of MRI findings in children included in the CP-EDIT cohort II. The type of MRI findings will be analysed and related to history, presence and type of CP and age of the child. Secondary results are to analyse if cranial ultrasound and/or CT is correlated to MRI findings.*Genetics.* A complete overview of pathogenic/likely pathogenic variants identified in the CP-EDIT cohort III and thus providing an overview of the genetic findings in an unselected cohort of children with suspected CP in a clinical setting.*GMA implementation.* Fidelity outcomes: Multifaceted training packages provided: (a) number, (b) content, (c) physiotherapists´ perspectives on the utility of sessions. Proportion of high-risk infants screened with GMA. Interrater reliability between the GMA assessors. Acceptability outcomes: Number of GMA videos (a) sent by parents, (b) made by physiotherapists. Additionally, assessment of physiotherapists´ confidence in providing a GMA score. The contextual factors change during the implementation process, these will be continually examined through observations and if relevant interview with stakeholders.*Prediction of CP*. The primary outcome is a confirmed diagnosis of CP “yes vs. no” at age 24 months. For infants defined as definite CP or high risk of CP, diagnosis will be confirmed by a neuropaediatrician according to the SCPE criteria [33]. Key secondary outcome: Motor function will be classified according to the Gross Motor Function Classification System (GMFCS), categorized into five levels from walking without limitation (level I) to non-ambulatory function (levels IV and V) [34]. For infants defined as unclear or definitely not CP, medical records will be reviewed for diagnosis and walking ability at the age of 24 months.*Diagnostic test accuracy study*. Infants at risk of CP will be assessed with sHAI, a 6-item structured video recorded play session of 5 min of duration. The test is performed in the clinic and assessed by a certified HAI assessor. A combination of MRI, GMA and/or HINE will be applied as the gold standard i.e., the high risk of CP or CP diagnosis reference standard.*GO-PLAY*. Patients referred to CP-EDIT trial will be randomized to receive either GO-PLAY intervention or standard care plus assessments. The primary outcome is improvement in motor development evaluated by Peabody Developmental Motor Scale 2 (PDMS-2) from baseline (T0) to the end of intervention (endpoint T6, 6 months post baseline. Key secondary outcomes will be HAI when the child is ≤ 12 months at the end of intervention, AIMS, Gross Motor Function Measure (GMFM-66), Bayley Scale of Infant and Toddler development 4, cognitive part (BSID-4, cog) and parental well-being. Neither the families nor the therapists responsible for intervention are blinded to group allocation. All outcome assessors will be masked to group allocation. The therapists responsible for data collection at each assessment point are not involved in the intervention, are unbiased as to group allocation, and have no access to previous assessments.*Parents perspectives on intervention.* Data are analysed using thematic analysis. Results from this study may support clinicians in understanding the parent’s perspectives and customize early home-based intervention to address parents’ expectations, concerns and needs in the Danish health care system.*Parents perspectives on early diagnosis.* Data are analyzed using thematic analysis approach, supported by investigator triangulation [35]. Findings are expected to be presented as themes and subthemes. This study may help clinicians to support the parent-infant interaction and tailor counselling to address parents’ experiences, concerns, and needs.

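### From 5 months, without an earlier abnormal GMA, a child can meet the 'Definitely CP' guide and still fail both entry routes to cohort III

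*Protocol article*

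**What the plan says.** All references are to the protocol article.

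- **Entry to cohort III** (The 3rd step). Children come from cohort II ("cohort III who have high risk of CP or definitely CP) if they fulfil at least one of the requirements A or B"). Route A is "any two of the following:A.1 Neuroimaging predictive of a motor disability", the other two items being absent fidgety movements on GMA and a HINE score below an age-specific cut-off. Route B needs both "B.1 Unilateral brain injury on neuroimaging (MRI or ultrasound") and clinical asymmetry.
- **'Definitely CP'** (same section). The definition "encompasses participants that fulfil SCPE CP clinical criteria and guided by fulfilling the following". The number of items asked for then depends on age, namely "4/5 for children < 5 months, and 3/4 for children ≥ 5 months of the following at screening". The five items are motor delay, GMA, HINE, a lesion on MRI or ultrasound in the route A structures, and focal signs or asymmetry.
- **Who cohort III is** (Cohort III). "Children with definite CP or high risk of CP", without qualification, seen at 6, 12, 18 and 24 months.
- **GMA by age** (Table 2; Cohort II). GMA is done below 5 months; from 5 to 12 months the motor tests are HAI and AIMS.
- **Imaging in CP** (Introduction). "CP remains a clinical diagnosis and MRI can be normal in a child with CP"; more than 80% of children with CP have abnormal imaging.
- **What depends on cohort III.** Blood for sequencing is taken on entry to it (Genetics), and GO-PLAY recruits from it at two sites (The 3rd step). The genetics outcome is presented as "an overview of the genetic findings in an unselected cohort of children with suspected CP in a clinical setting".

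**The concern.** The entry rule and the definition weigh the same findings differently. Motor delay counts towards 'Definitely CP' but towards neither route. Focal signs count towards entry only as asymmetry, and only alongside a unilateral lesion. Once GMA is no longer available, a child can collect enough points for the definition without satisfying either route, and no sentence admits a 'Definitely CP' child automatically.

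The affected children are older infants, the group in which the Discussion says little has been published. If the text is followed as written, older infants without an abnormal GMA enter cohort III only with a lesion. Sequencing yield and the GO-PLAY population would then be conditional on imaging in that age group without the article saying so. The Introduction notes that a genetic cause is often found in children without gestational or neonatal risk factors, so this selection could bear on the yield; the documents do not show in which direction. Two sites could also allocate the same child differently.

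**Working it through.** **Inputs.** D = motor delay, G = absent fidgety movements, H = HINE below cut-off, M = lesion in the listed structures, F = focal signs or asymmetry. U = unilateral injury predictive of CP, S = clinical asymmetry. Three assumptions: U is counted only together with M; S is counted only together with F; and the item that drops out at 5 months is G, which is inferred from the GMA schedule.

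**Rules.** Route A: G + H + M ≥ 2. Route B: U and S. Definite below 5 months: D + G + H + M + F ≥ 4. Definite from 5 months: D + H + M + F ≥ 3.

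**Below 5 months.** Only D and F lie outside route A, so any four items include at least 4 − 2 = 2 route A items. Counting U and S, 20 profiles qualify as definite and 0 fail entry.

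**From 5 months, no abnormal GMA.** With G = 0, route A becomes H and M. Route B always needs imaging.

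| Items met | Profiles (with U, S) | Route A | Route B | Fail both |
|---|---|---|---|---|
| D, H, M | 2 | yes | – | 0 |
| H, M, F | 4 | yes | – | 0 |
| D, H, M, F | 4 | yes | – | 0 |
| D, H, F (no lesion) | 2 | no (1 of 2) | impossible | 2 |
| D, M, F (HINE above cut-off) | 4 | no (1 of 2) | only if U and S | 3 |

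The total is 2 + 4 + 4 + 2 + 4 = 16 profiles, of which 2 + 3 = 5 fail both routes. The three failures in the last row are: no unilateral lesion and no asymmetry; asymmetry without a unilateral lesion; and a unilateral lesion without asymmetry. These are counts of logical profiles, not of children, and carry no frequency weight.

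**With an abnormal GMA on file.** Setting G = 1 gives H + G = 2 or M + G = 2, so all five failing profiles enter by route A.

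**Size.** The plan's 160 (Sample size estimation) is reproduced by 20 new patients × 4 centres × 2 inclusion years = 160, if 20 is read as a yearly figure. For the normal-imaging profile:

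number = 160 × (share with normal imaging) × (share presenting at 5 months or more)

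- Normal imaging: below 20%, from the more-than-80% statement. The lower end of 5% is an assumption.
- Presenting at 5 months or more: one third (the expected infant-pathway share of cohort II) to one half (the Discussion's share of CP discernible later in infancy). Both are proxies; neither is a stated share of CP cases by age.

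Low: 160 × 0.05 × 1/3 = 2.7. High: 160 × 0.20 × 1/2 = 16. The sum treats every such child as having delay, low HINE, focal signs and no abnormal GMA. It leaves out the D, M, F gap, for which the document gives no figure.

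**The case against.** The strongest reply is that the item count is only a guide. The SCPE clinical criteria are the requirement, and local steering groups place each child (Study design and methods). The definition also follows the entry rule in the text, so it can be read as sorting children already admitted into definite and high-risk. On that reading nobody labelled definite is turned away.

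Part of this stands: the count is not binding, and practice may be more flexible than the text. But the A/B rule carries no such latitude, and under the sorting reading a child with the same findings and no lesion is still outside cohort III. The MRI objective also describes cohort II as being divided into definite, high-risk, unclear and not CP, which suggests that the label is not reserved for children already admitted.

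A reader might infer more than the documents support:

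- *That CP with normal imaging is shut out altogether.* It is not. Absent fidgety movements plus a low HINE satisfy route A with normal imaging, and below 5 months there is no gap.
- *That the upper end of the range is an expected loss.* It rests on 20% normal imaging, which is a ceiling.
- *That these children lose the 24-month outcome in the prediction study.* The outcome section ties neuropaediatric confirmation to being classed as definite or high-risk CP, not to cohort III membership. What is lost is the scheduled cohort III visits.
- *That the GO-PLAY comparison is biased.* Randomisation follows entry, so its internal validity and sample size are untouched; only the population it describes is affected.

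Cohort III is in any case selected on definite or high-risk CP, so 'unselected' was already loose. What remains is that the further selection on imaging is undeclared.

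**Conclusion.** The point holds for children first assessed at 5 months or more with no earlier abnormal GMA. For them the entry rule and the 'Definitely CP' guide disagree, and the Cohort III section describes a group that the entry rule does not deliver. Five of 16 qualifying profiles fail both routes at that age; none of 20 does below 5 months. This is a matter of logic and does not depend on any count of patients. The number of children is not in the document; about 3–16 of 160 is an illustration for the normal-imaging profile under the assumptions shown. The defect concerns who is followed, sequenced and offered GO-PLAY, and how those results may be described. It warrants correction, but it does not undermine the randomised comparison or the 24-month diagnosis.

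**What to change.** Reconcile the A/B entry rule, the 'Definitely CP' definition and the Cohort III section. Either of two statements would do it:

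- state that children classed as 'Definitely CP' belong to cohort III; or
- state that from 5 months, without an earlier abnormal GMA, cohort III, the genetic yield and GO-PLAY apply to infants with an imaging lesion, and drop 'unselected' from the genetics outcome. With this option the D, M, F profile still needs an explicit ruling, because those infants have a lesion and fail entry on other grounds.

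The choice is for the investigators. The text change is a sentence or two, but it is a protocol change, to be notified to the ethics committee and registry as the article provides. Including all 'Definitely CP' children may add a few infants to follow-up and sequencing, and to GO-PLAY at its two sites. Declaring the imaging restriction adds none but narrows the stated population.
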